### Moderators of outcome measures

Several potential moderators of the outcome variables will be assessed. The Massachusetts Youth Screening Instrument version 2 [89] is a self-report questionnaire that screens for a multitude of behaviour problems and potential emotional distress. The Pubertal Development Scale [90] is used to assess pubertal stage using words, rather than pictures, in those participants aged 12 years and above. The Social and Health Assessment scales [91]—specifically the subscales that relate to peers and neighbourhood environment, but also those that assess alcohol and drug use, bullying and future outlook—are used in the present study. To assess intelligence quotient (IQ), two sub-tests of the Wechsler Intelligence Scale for Children, Fourth Edition [92], or the Wechsler Adult Intelligence Scale, Fourth Edition, are performed with the adolescents: vocabulary as a measure of verbal comprehension and matrix reasoning to examine perceptual reasoning capacity. The Diagnostic Interview for DSM-IV Personality Disorders (Axis II [93]) is a semi-structured diagnostic interview done to assess the ten DSM-IV personality disorders. In the present study, a sub-section is used to assess borderline personality disorder symptoms. The quality of the youth welfare institution is systematically assessed through use of the Institutional Quality Index (IQI). The Treatment as Usual Questionnaire (TAU-Q) is distributed to assess the youth welfare institution’s standard care. Both the IQI and TAU-Q were developed specifically for the purpose of the present study. The Childhood Experience of Care and Abuse Questionnaire [94] is a self-report questionnaire that was developed to mirror an existing validated interview measure: the childhood experience of care and abuse. The questionnaire assesses lack of parental care (neglect and antipathy), parental physical abuse, and sexual abuse from any adult before age 17 years. Information regarding pre-natal and peri-natal risk factors for antisocial behaviour, such as maternal smoking in pregnancy, post-natal depression and negative living conditions in early life, as well as the socio-economic status, is additionally assessed during a standardised interview with primary caregivers. For a detailed overview on measurement time points/trial schedule, please refer to the Standard Protocol Items: Recommendations for Interventional Trials (SPIRIT) checklist shown in Fig. 2. For a detailed overview on information given within this protocol please consult (Additional file 2).

**Fig. 2 Fig2:**
[figure not shown]
Standard Protocol Items: Recommendations for Interventional Trials (SPIRIT) checklist for the trial. *ANS* Autonomic nervous system, *ARI* Affective Reactivity Index, *BMSLSS* Brief Multidimensional Students’ Life Satisfaction Scale, *BSQ* Burnout Screening Scale, *CBCL* Child Behaviour Checklist, *CD* Conduct disorder, *CECA-Q* Childhood Experience of Care and Abuse Questionnaire, *CSQ* Client Satisfaction Questionnaire, *DERS* Difficulties in Emotion Regulation Scale, *DIPD-IV* Diagnostic Interview for DSM-IV Personality Disorders, *EMA* Ecological momentary assessment, *fMRI* Functional magnetic resonance imaging, *GAS* Goal Attainment Scaling, *HR* Heart rate, *HRV* Heart rate variability, *ICU* Inventory of Callous-Unemotional Traits, *IQ* Intelligence quotient, *IQI* Institutional Quality Index, *K-SADS-PL* Kiddie Schedule for Affective Disorders and Schizophrenia for School-Age Children–Present and Lifetime, *MOAS* Modified Overt Aggression Scale, *ODD* Oppositional defiant disorder, *QAF* Quality Assurance Form, *RSA* Respiratory sinus arrhythmia, *SCL* Skin conductance level, *SCR* Skin conductance response, *T1, T2, T3, T4* Time points 1, 2, 3 and 4, *TAU* Treatment as usual, *TAU-Q* Treatment as Usual Questionnaire, *TSQ* Training Satisfaction Questionnaire, *WAIS* Wechsler Adult Intelligence Scale, *WISC-IV* Wechsler Intelligence Scale for Children, Fourth Edition, *YPI* Youth Psychopathic Traits Inventory, *YSR* Youth Self-Report

### Neurobiological measures of emotion processing

#### Neuropsychological correlates

The emotional go/no go task [95] will be used to examine regulation under multiple emotional conditions, including positive, negative and neutral facial expressions. With the Passive Avoidance Learning Test, we intend to assess stimulus-reinforcement learning (adapted from [96]).

#### Autonomous correlates

Autonomous correlates will be measured as part of a neuropsychological test battery. Basal autonomic nervous system (ANS) parameters will be measured during a 5-minute resting protocol [97]. ANS reactivity will be measured during a countdown task [98] and while watching emotion-evoking film clips [99]. Especially HRV seems to be a promising indicator of treatment success [67, 100].

#### Neural correlates

Neural correlates will be studied using functional and structural magnetic resonance imaging at baseline. Changes in these neural correlates will be investigated (in a sub-sample post-intervention in Basel and Aachen only) as mechanisms underlying the brain’s adaptation to treatments likely related to both structural plasticity and functional response alterations [101].

#### Genetic functional variants

Genetic functional variants in saliva (serotonergic, noradrenergic, dopaminergic, neuropeptide) will be investigated to test the hypothesis that specific functional genetic variants are predictive of low intervention success.

### Sample size calculation and statistical analysis

The sample size calculation is based on the primary efficacy endpoint ‘pre-post treatment change in number of fulfilled CD/ODD diagnostic criteria’ after the 12-week group-based START NOW training programme for female adolescents (as add-on therapy to TAU) compared with TAU only within youth welfare institutions. On the basis of results reported by Nelson-Gray et al. [54], pre-post changes in the treatment group of μ = 3 and in the control group of μ = 1, as well as a conservative common standard deviation of 3.5 for both groups, are expected. Because the Nelson-Gray et al. study intervention comprised only 1 DBT training module and only 16 sessions instead of 14 group sessions + 12 individual sessions as in our study, compared with the change of 2.24 in the Nelson-Gray study, we expect at least μ = 3. In addition, it has to be assumed that TAU in youth welfare settings will also result in reduction of ODD/CD symptoms. Owing to the group therapy and the respective appropriate randomisation procedure, we will have a correlated data structure. To account for that, a design effect of 1.08 to adjust for intra-group correlation of 0.02 is assumed. To achieve a power of 80% (α = 5%, two-sided; two-sample *t* test), a total of 108 patients is required for the analysis. Therefore, 172 patients will be assessed for eligibility to obtain 128 patients to be randomised (assuming that 25% of screened patients are not eligible). A drop-out rate of 15% is expected (including major protocol violations and loss to follow-up). The problem of missing values is partly resolved in the confirmatory analysis by application of an imputation strategy. Nevertheless, another 15% of patients will be randomised to compensate for the loss of information caused by drop-outs and loss to follow-up. The sample size calculation was done using nQuery Advisor 7.0 software (Statistical Solutions, Cork, Ireland).

### Statistical methods

The full analysis of the primary outcome measure will be conducted on the basis of the intention-to-treat (full analysis set) population, including all randomised patients. To account for the data structure, a linear mixed model with the primary endpoint (change in ODD/CD score between baseline and end of intervention) as the response variable, including baseline CD/ODD symptoms, group, age, site and IQ as fixed factors and the respective cluster as a random factor, will be applied. The random intercept, as well as the residuals, will be assumed to be normally distributed. The correlation structure can be referred to as compound symmetry [102], which is a common assumption in cluster-randomised trials [103]. The results will be presented as the mean between-group difference with the corresponding two-sided 95% confidence interval. The associated Hedges’ effect size *g* [104] will be calculated, in addition to the practice-related intra-cluster correlation coefficient. To fit the primary model, the restricted maximum likelihood approach will be used.

The overall type I error rate is set at α = 5% (two-sided) and will be controlled by applying the multiple test procedure for hierarchically ordered hypotheses. The first null hypothesis states that the change in ODD/CD score between baseline and end of intervention is equal for both the intervention and control groups (H_0I_: μ_1I_ = μ_2I_). This hypothesis will be tested at a two-sided level of significance of 5% against the alternative hypothesis (H_1I_: μ_1I_ ≠ μ_2I_). Only if the first hypothesis can be rejected will the second null hypothesis, which states that the change between baseline and follow-up (12 weeks after end of intervention) will be equal in both groups (H_0II_: μ_1II_ = μ_2II_), be tested in the same way. This second hypothesis can then be tested also at a two-sided level of significance of 5% against the alternative hypothesis (H_0II_: μ_1II_ ≠ μ_2II_). Application of this multiple test procedure for hierarchically ordered hypotheses assures control of the overall type I error rate of 5%. Both null hypotheses will be tested by applying a random effects model that includes baseline CD/ODD symptoms, group, age, institution and IQ as fixed factors and cluster as a random factor. This statistical analysis plan was specified before the opening of the database.

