**Methods/design:**

The study is a prospective, confirmatory, cluster-randomised, parallel-group, multi-centre, randomised controlled trial with 128 institutionalised female adolescents who fulfil the diagnostic criteria of ODD and/or CD. Institutions/wards will be randomised either to provide the 12-week skills training as an add-on intervention or to provide treatment as usual. Once the first cycle is completed, each institution will run a second cycle with the opposite condition. Primary endpoints are the pre-post change in number of CD/ODD symptoms as assessed by a standardised, semi-structured psychiatric interview (Kiddie Schedule for Affective Disorders and Schizophrenia for School-Age Children–Present and Lifetime, CD/ODD section) between baseline and the end of intervention, as well as between baseline and a 3-month follow-up point. Secondary objectives include pre-post change in CD/ODD-related outcome measures, most notably emotional regulation on a behavioural and neurobiological level after completion of START NOW compared with treatment as usual.

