## Methods/design

The present study is a prospective, confirmatory, cluster-randomised, multi-centre, international phase III trial with two parallel groups (intervention vs. TAU) and three trial phases (baseline assessment, 12 weeks of treatment, 12 [±1] weeks of follow-up observation). The intervention condition is incorporated into the usual standard care within residential care (START NOW + TAU) vs. TAU. A randomised controlled AB-BA design will be used. Institutions will be randomised to start either with the intervention group (A) or with the control group (B) (TAU). After having conducted A or B, each institution will run the other condition: Institutions starting with TAU receive START NOW, and institutions that finished START NOW and the follow-up assessment conduct a new group with TAU, whereby strict rules are defined to eliminate the risk of carry-over effects.

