### Study centres

The study will take place at youth welfare institutions located in proximity to four clinical trial centres. Study centres include the departments of child and adolescent psychiatry at the university hospitals in Basel, Switzerland (CS, principal investigator); Frankfurt, Germany (CMF); Aachen, Germany (BHD); and Amsterdam, The Netherlands (AP). Data management as well as biometric and statistical support are provided by the Institute of Medical Biometry and Informatics (IMBI), University of Heidelberg, Germany. The Coordination Centre for Clinical Trials (Koordinierungszentrum für Klinische Studien [KKS]) at the University of Heidelberg is in charge of study monitoring.

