Essential methodological issues will be considered to manage threats to internal validity on the outcome of the present randomised controlled trial [108]. START NOW is manualised, and all facilitators receive 2 days of rigorous, standardised training. Beyond an in-depth preparation, START NOW’s implementation will be checked via regular fidelity monitoring assessed by the respective supervisor through use of a standard QAF. The study is large enough to determine the presence of clinically important effects, and mediators and moderators of response will be investigated. Our primary outcome measure is based on a clinical interview conducted by independent observers with both the adolescent and a (non-involved) social worker. In doing so, we gather comprehensive information that does not rely on a sole source and combines interview information, file information and clinical judgement to reach a final conclusion. Furthermore, the fact that we continuously collect neurobiological and neuropsychological data presents a major advantage because we will subsequently be able to combine and compare these objective indicators with the clinical data collected. Procedurally, the randomised AB-BA design is a further benefit because it will enable us to assess within-institution effects. This point is of particular importance because youth welfare institutions vary extremely with regard to size, type of population served, organisational and structural aspects, financial resources, and professional training opportunities. The automated online randomisation procedure is clearly defined and reflects the study design. The statistical analysis takes the different study centres and institutions into account. Furthermore, a strong advantage of the present study is the 3-month follow-up period to investigate long-term effects of the intervention.

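### The confirmatory mixed model is stated in two incompatible ways (site fixed or institution fixed), with 'cluster' not tied to one unit and no cycle term for the AB-BA design

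*Protocol article*

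**What the plan says.** Statistical methods, first paragraph, gives the model for the change from baseline to end of intervention as a linear mixed model "including baseline CD/ODD symptoms, group, age, site and IQ as fixed factors and the respective cluster as a random factor". It has one normally distributed random intercept, compound symmetry and restricted maximum likelihood.

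The second paragraph sets out the two ordered hypotheses, H0I (end of intervention) and H0II (follow-up), and then says: "Both null hypotheses will be tested by applying a random effects model". The terms it lists are "baseline CD/ODD symptoms, group, age, institution and IQ as fixed factors and cluster as a random factor". Since this covers both hypotheses, it covers H0I, the test already modelled in the first paragraph.

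The levels are distinct. Under Study centres: "The study will take place at youth welfare institutions located in proximity to four clinical trial centres". Methods against bias adds that randomisation is stratified by site. On the design, Methods/design says "A randomised controlled AB-BA design will be used" and "After having conducted A or B, each institution will run the other condition". The Discussion says that "the randomised AB-BA design is a further benefit because it will enable us to assess within-institution effects", and also that the analysis allows for both centres and institutions.

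The clustered unit appears under several names:
- Abstract: "Institutions/wards will be randomised either to provide the 12-week skills training as an add-on intervention".
- Methods against bias: institutions randomised in groups of four to eight.
- Sample size section: an intra-group correlation.
- Statistical methods: a practice-related intra-cluster correlation, although the trial has no practices.

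**The concern.** Two fixed-effect lists for one confirmatory test leave the analyst to choose, and the choice changes the standard error and the reference distribution. It cannot be settled from the text, because the meaning of the random term is open as well.

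Each institution contributes two therapy groups, one per condition, in successive cycles. Three things then matter: whether girls in the same therapy group are allowed to be more alike than girls from the same institution in different cycles, whether treatment is compared within institutions, and whether calendar drift between cycles is separated from the condition effect. The two versions answer the first two differently, and neither addresses the third.

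This is not detail that an article leaves to a fuller document. The article lists the fixed and random terms, the correlation structure and the estimation method, and describes them as the analysis plan. The problem lies in what it states.

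**Working it through.** **1. The plan's own figures.** Inputs from the sample size section: difference 3 − 1 = 2, SD 3.5, two-sided 5%, power 80%, design effect 1.08, intra-group correlation (ICC) 0.02, drop-out 15%.
- Two-sample t test: 49 per arm gives power 0.7996 and 50 gives 0.808, so 50 per arm.
- 50 × 1.08 = 54 per arm, 108 in total, as stated.
- 108 / 0.85 = 127.1, consistent with 128 randomised.
- Implied group size: (1.08 − 1) / 0.02 + 1 = 5.

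The sample size is not at issue.

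**2. What each reading implies.**

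| | Cluster = institution | Cluster = therapy group |
|---|---|---|
| Paragraph 1 (site fixed) | Same-group and cross-cycle girls equally correlated; extra group-level variation ignored | No institution term; within-institution pairing not used |
| Paragraph 2 (institution fixed) | Random intercept duplicates the fixed factor; its variance cannot be estimated separately | Workable; treatment compared within institutions |

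**3. Size at ICC 0.02.** The number of institutions is not given. Assumption: 108 / (2 cycles × 5 girls) = 10.8, so 11 institutions and 110 girls. Simulation of a balanced analysis-of-variance layout: total SD 3.5, 200,000 runs per scenario, variance estimates truncated at zero, t reference with the degrees of freedom of the relevant stratum, six AB and five BA institutions, no cycle effect. The ICC is split equally between institution and group.

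| Reading | Type I error | Power at difference 2 |
|---|---|---|
| Cluster = institution | 0.055 | 0.845 |
| Site fixed, cluster = group | 0.031 | 0.759 |
| Institution fixed, cluster = group | 0.023 | 0.716 |

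Placing the whole 0.02 at group or at institution level keeps type I error between 0.021 and 0.061.

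**4. Higher ICC (assumed).** With ICC 0.10 split equally, cluster = institution gives type I error 0.078. With all of it at group level, it gives 0.105. The two readings with cluster = group stay between 0.030 and 0.044.

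**5. Missing cycle term.** With complete cycles, bias = (BA − AB) / (AB + BA) × cycle effect, where AB and BA are the numbers of institutions in each sequence.
- 6 AB, 5 BA: −1/11 = −0.09 per symptom of cycle effect.
- 8 AB, 3 BA: −5/11 = −0.45 per symptom. With an assumed one-symptom effect, a true difference of 2.0 is estimated at about 1.54.
- Near balance there is still a power cost. At ICC 0.10 split equally, 6:5, one-symptom effect, institution fixed and cluster = group, power is 0.584 without a cycle term and 0.668 with it.

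**6. Power of one explicit model** (institution and cycle fixed, therapy group random). Closed form at ICC 0.02 split equally, with σ² = 3.5² = 12.25:
- Variance of the contrast = 2 × (0.01 × 12.25 + 0.98 × 12.25 / 5) / 11 = 2 × (0.1225 + 2.401) / 11 = 0.459; SE 0.677.
- Without cycle: 10 degrees of freedom, critical value 2.228, power 0.76.
- With cycle at 6:5: SE = 0.677 / √(1 − (1/11)²) = 0.680, 9 degrees of freedom, critical value 2.262, power 0.74.
- Simulated with estimated, truncated variances: 0.68 to 0.71, depending on the split of the ICC.

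Sensitivity to the assumed number, using the stated group sizes with 15% drop-out (same formula, cycle included, equal sequences):
- 128 / (2 × 8) = 8 institutions with 6.8 analysed girls per group: 6 degrees of freedom, power 0.68.
- 128 / (2 × 4) = 16 institutions with 3.4 per group: 14 degrees of freedom, power 0.79.

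**The case against.** The strongest defence is that 'cluster' can be inferred. The sample size section attributes the correlation to group therapy and calls it intra-group, the design effect implies groups of five, and randomisation is in groups of four to eight. A random cluster beside a fixed institution can only be estimated if the two differ. On that reading the second paragraph is already close to a sound model and lacks only a cycle term. This stands, and it limits the point: the second paragraph is workable under one definition. It does not remove the first paragraph, which gives a different list for the same test, and the text never says which definition is meant.

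Two stronger readings are tempting.
- **A reader might infer that the planned test is seriously anticonservative.** The documents do not support this. It requires cluster to mean institution and a group-level ICC well above the planned 0.02.
- **A reader might infer that the treatment estimate will be biased by time.** Methods against bias requires a gap of more than six months before a second TAU cycle, but only where START NOW participants remain in the same living group. Trial status gives January 2017 only as the expected end of recruitment. Nothing says that second cycles will be missed or that symptoms drift. With balanced, complete cycles the bias is small.

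It is also fair that the choice of degrees-of-freedom method and the handling of period effects are often left to a fuller plan. They appear here as part of the remedy; their absence is not itself the error.

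**Conclusion.** The point holds as a contradiction in the stated confirmatory model. H0I has two incompatible fixed-effect lists, and the random unit is not identified. That part needs no assumption.

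The numerical consequence is moderate. At the planned ICC the choice of reading moves type I error only between about 2 and 6%, but moves power between about 0.72 and 0.85 on an assumed 11 institutions, two cycles and five girls per group. Larger type I distortion depends on higher assumed ICCs. The missing cycle term is a secondary weakness whose effect depends on imbalance or missing second cycles together with a time trend, neither of which can be sized from the article.

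**What to change.** Before outcomes are examined by condition, replace the two descriptions with one model for H0I and H0II:
- Define the cluster as the institution-by-cycle therapy group, and use that term throughout, including for the reported intra-cluster correlation.
- Fixed: condition, cycle (first or second), baseline CD/ODD count, age, IQ and institution. Institution absorbs site.
- Random: therapy group.
- Small-sample degrees of freedom, for example Kenward-Roger.

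A model with site fixed and both institution and institution-by-cycle random is a legitimate alternative. The two are not equivalent when an institution completes only one cycle, because the random version recovers between-institution information. One must therefore be chosen in advance.

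No new data are needed, but the cost is more than wording. With about 11 institutions the treatment contrast has only about 9 to 10 degrees of freedom, and power may be roughly 0.68 to 0.76 rather than 80%. The power statement should be redone for the chosen model with the actual number of institutions.
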